#### Adjusted analysis

Using appropriate descriptive statistics, we will assess any imbalance between the trial arms at baseline and describe the characteristics of participants. As participants are randomised using the method of minimisation we are not expecting significant imbalance between groups. However, the minimisation variables (age, gender, SPPB) will be adjusted for in the statistical analysis.

### MRI imaging sub-study

#### Primary and secondary outcome data analysis

The primary analysis will be based on an intention-to-treat (ITT) principle. The primary outcome (change in adjusted hippocampal volume) will first be examined using a one-way analysis of variance (ANOVA) with group (exercise, control) as a between-subjects factor. An analysis of covariance (ANCOVA) model will then be carried out with the primary outcome as output, group as main factor, and age group, gender and education as covariates. If there is a main effect of group, single-sample *t* tests will be conducted to assess whether the rate of change in hippocampal volume differed from 0.

The secondary cognitive and behavioural outcomes will also be modelled using ANCOVAs. For the MRI secondary outcomes, specialised neuroimaging techniques, including non-parametric methods, will be employed. To examine the correlations between change in hippocampal volume and change in relational memory, Pearson’s correlations will be calculated.

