#### Model assumptions

For all methods outlined, underlying assumptions will be checked using standard methods, e.g. residual plots. If assumptions are not valid then alternative methods of analysis will be sought. In particular, the underlying assumption of the linear impact of baseline covariates will be assessed and, if necessary, baseline covariates will be categorised and fitted as factors in the model. Age, gender and SPPB will be adjusted for in the statistical analysis.

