#### Subgroup analyses

We will compare response to exercise based on SPPB score (ranges 4–7 and 8–9), adherence (high-low), age categories (65–74, 75 + years), gender and cognition (MoCA < 26 > 26, 26 + years).

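### The MRI sub-study tests its primary outcome by ANOVA and then ANCOVA without naming a lead, and its two covariate lists do not match; one pre-specified ANCOVA would settle both.

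*Protocol article*

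**What the plan says.** All of this stands under the heading MRI imaging sub-study in the Protocol article.

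- **First test.** Under Primary and secondary outcome data analysis, the outcome to be tested is the change in adjusted hippocampal volume. The article says that it "will first be examined using a one-way analysis of variance (ANOVA) with group (exercise, control) as a between-subjects factor".
- **Second test.** The next sentence continues: "An analysis of covariance (ANCOVA) model will then be carried out with the primary outcome as output". The terms of that model are given as "group as main factor, and age group, gender and education as covariates".
- **Follow-on tests.** Single-sample t tests on the rate of change come next, on a condition: "If there is a main effect of group". The model that supplies this effect is not named.
- **Second covariate list.** Under Model assumptions: "Age, gender and SPPB will be adjusted for in the statistical analysis". The same section allows recoding if linearity fails: "if necessary, baseline covariates will be categorised and fitted as factors in the model".

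Three other parts of the article bear on this. Randomisation/allocation gives the minimisation factors as study site, age group, gender and initial SPPB score. Adjusted analysis, in the main-trial part, commits to adjusting for age, gender and SPPB because they are minimisation variables. Table 2 schedules the MRI scan at baseline, 6 and 12 months.

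**The concern.** The sub-study has one primary outcome but two group tests of it, in sequence, with no statement of which answers the question. The two can disagree, and the article gives no rule for that case. The condition on the t tests inherits the same gap, since a group effect might appear in one model and not in the other.

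The covariates are also unsettled. Education is only in the first list, SPPB only in the second, and age is a category in one and plain age in the other. The ANOVA adjusts for none of the minimisation factors, although the article gives minimisation as its reason for adjusting in the main trial. The main trial adjusts for the baseline value of its own outcome; the sub-study does not, although it collects that value.

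At stake is whether the sub-study has one answer fixed in advance, together with a little precision.

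**Working it through.** **1. Is there a figure of the plan's own to reproduce?** The article gives no sample size, effect size, SD or alpha for the MRI sub-study. The main-trial sample size (Sample size calculation) reproduces: a difference of 0.5, SD 2.0, two-sided 5% and 85% power need 288 evaluable per arm, and 288 / 0.75 = 384. The point does not depend on it.

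**2. The models side by side.**

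| Term | ANOVA | ANCOVA (outcome section) | Model assumptions section |
|---|---|---|---|
| Age | no | yes, as group | yes, form not given |
| Gender | no | yes | yes |
| SPPB | no | no | yes |
| Education | no | yes | no |
| Baseline hippocampal volume | no | no | no |
| Named as lead | no | no | not applicable |

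**3. Type I error if either the ANOVA or the ANCOVA could be claimed.** Assumption: the covariates explain a share R² of the variance in change. Under the null the two z statistics then correlate at about √(1 − R²), and the probability wanted is that at least one exceeds 1.96 in absolute value (bivariate normal).

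| Assumed R² | Correlation | P(either significant) |
|---|---|---|
| 0.02 | 0.990 | 5.7% |
| 0.05 | 0.975 | 6.0% |
| 0.10 | 0.949 | 6.5% |
| 0.20 | 0.894 | 7.1% |
| 0.30 | 0.837 | 7.6% |

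**4. Check by simulation.** 8,000 null data sets per setting, total N of 60, 100 or 200, and total R² of 0.1, 0.3 or 0.5 split equally over age, gender, education and SPPB (all assumed). Allocation was 1:1 and minimisation was not modelled.

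- One model fixed in advance: 4.5% to 5.7%, that is, the nominal 5% within simulation error.
- Better of the ANOVA and the ANCOVA in the outcome section: 6.0% to 8.0%.
- Best of three, adding an ANCOVA with age, gender and SPPB: 6.8% to 10.1%.

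The inflation is limited because the tests are highly correlated. Independent tests would give 1 − 0.95² = 9.75% for two and 1 − 0.95³ = 14.3% for three.

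**5. Precision from baseline volume.** Let r be the correlation between baseline and follow-up volume, with equal variance σ² at both. Apart from a common factor for sample size, the variance is 2σ²(1 − r) for a change-score analysis and σ²(1 − r²) for ANCOVA on baseline. The ratio is (1 + r)/2.

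- r = 0.90: ratio 0.95, a 5% saving.
- r = 0.98: ratio 0.99, a 1% saving.

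Both values of r are assumptions. A chance baseline difference d carries into the change score as about (1 − r)d, so only 2% to 10% of it remains.

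**The case against.** The other side has a good case on several points.

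**An unadjusted test followed by an adjusted one is ordinary practice.** Both are announced, in a fixed order, and a statistical analysis plan that is not shown may name the lead. That limits the point. A reader might infer that the plan allows success to be claimed on whichever test is significant, but the article states no such rule. The 6.5% to 7.6% therefore describes what a free choice would cost, not the error rate of the plan, and at R² of 0.02 to 0.05 it falls to 5.7% to 6.0%.

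**The covariate lists may be additive.** Neither says that it is exhaustive, and the sentence under Model assumptions repeats the main-trial commitment. Taken together they give age, gender, education and SPPB. That reading is possible and would remove the conflict, but the article does not state it, and the ANCOVA sentence reads as a full specification without SPPB.

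**Baseline volume already enters through the change score.** This stands: the gain is small, and omitting it does not by itself create a choice of results.

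Three stronger readings are tempting but not supported.

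- *That the present analysis is biased.* Under randomisation the change-score ANOVA and the ANCOVA are both unbiased.
- *That the 6-month scan is unused.* The article does not define the interval for change, and it speaks of a rate of change. A slope per person over 0, 6 and 12 months would use that scan and could still go into a one-way ANOVA.
- *That a MoCA score of 26 falls in no subgroup.* The line reads "cognition (MoCA < 26 > 26, 26 + years". It is garbled, but it contains 26 and above, so the natural reading is below 26 against 26 or more.

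**Conclusion.** The point holds as one of specification. The article gives two tests of the sub-study's primary outcome with no lead, a condition on the t tests that names no model, and two covariate lists that do not match as printed. The first test ignores the minimisation factors, and no model uses baseline hippocampal volume as a covariate.

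The practical size is modest. The main gain is one answer fixed in advance and consistent with the minimised randomisation. Added to that is a variance saving of about 1% to 5%, if the test-retest correlation is 0.98 to 0.90. The type I error figures rest on an assumed R² and on a claim rule that the article does not contain. An unseen analysis plan might name the lead, but the two printed lists would still need to be reconciled. Only the MRI sub-study is affected, not the SPPB comparison at 24 months.

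**What to change.** - Name one lead analysis for the sub-study: an ANCOVA of hippocampal volume, or of its change, on group, adjusted for baseline hippocampal volume, age, gender, baseline SPPB and education.
- Print that same list under Primary and secondary outcome data analysis and under Model assumptions, with age in one form.
- Keep the unadjusted ANOVA as a supportive analysis.
- State that the single-sample t tests depend on the group effect from the lead model.

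The cost is wording only. Table 2 schedules the baseline scan and SPPB, and demographic and social data are taken at telephone screening. Table 2 does not list education by name, but the article already plans to use it as a covariate here and in the main-trial subgroups. No new data or visits are needed. The change should be made before anyone sees sub-study outcomes by arm.

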## Methods

### Trial design

The study protocol is presented in accordance with the Standard Protocol Items: Recommendations for Interventional Trials (SPIRIT) guidelines (Additional files 1 and 2).

The REACT study is a multi-centre, pragmatic, two-arm, parallel-group randomised controlled trial with an internal pilot phase and that incorporates comprehensive process and economic evaluations. Following identification and recruitment, 768 participants who meet the study inclusion criteria will be randomised to receive either the REACT intervention, delivered over a period of 12 months by trained facilitators or a minimal control intervention. The pilot phase will assess the feasibility of recruitment methods (allowing for some refinement if needed) and confirm adequate retention rates in the intervention and the study, prior to progressing with the main trial. A nested sub-study, led by the Wellcome Centre for Integrative Neuroimaging, University of Oxford, employing magnetic resonance imaging (MRI), will test the hypothesis that the REACT intervention will slow the rate of brain atrophy and of decline in cognitive function. Outcome data will be collected at baseline, 6, 12 and 24 months for the main study, with MRI sub-study data collected at baseline, 6 and 12 months. The REACT study was reviewed and approved by the National Health Service (NHS) South East Coast-Surrey Research Ethics Committee (15/LO/2082). The study is registered as a current randomised controlled trial (ISRCTN45627165).

The REACT study will be conducted at three UK sites – Bath/Bristol, Devon and Birmingham – allowing recruitment of a socio-economically and ethnically diverse sample including participants from urban, rural and semi-rural locations.

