### Randomisation/allocation

When 30 eligible participants have been recruited (enough to form one study group) they will be randomised to one of the two arms (physical activity (intervention) arm or social and education (control) arm using a secure, centralised, web-based randomisation website built by Peninsula Clinical Trials Unit (CTU). Randomisation will be performed using a minimisation algorithm to balance groups in terms of study site (Bath/Bristol, Birmingham, Exeter/Devon), age group, gender and initial functional ability (SPPB score). This algorithm has been built by the Peninsula CTU and uses the method proposed by Taves and extended by Pocock et al. [15, 16]. It maintains a stochastic element by computing probabilities proportional to the existing imbalance at the point of randomisation.

During the pilot phase, the randomisation will be 2:1 (intervention/control) in order to enable feasibility testing of intervention engagement and retention as early as possible. The main trial randomisation will be 1:1. Couples presenting together at the screening where both people are eligible and willing to be involved in the study will be randomised together to reduce contamination between study arms.

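### MRI sub-study: the hippocampus–memory association is specified as a plain Pearson correlation, with no adjustment for or split by arm, although the intervention is expected to move both measures

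*Protocol article*

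**What the plan says.** All of the relevant text is in the Protocol article.

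- **MRI imaging sub-study, Primary and secondary outcome data analysis:** Pearson's correlations are planned "To examine the correlations between change in hippocampal volume and change in relational memory". The sentence names no covariates, no significance level and no causal reading. It does not say whether the arms are pooled or taken separately.
- **Same section, models for the two measures:** hippocampal change is first compared by a one-way ANOVA on group, then by an ANCOVA with "group as main factor, and age group, gender and education as covariates". For the cognitive side, "The secondary cognitive and behavioural outcomes will also be modelled using ANCOVAs".
- **MRI imaging sub-study, Model assumptions:** the section opens with "For all methods outlined, underlying assumptions will be checked using standard methods, e.g. residual plots" and closes with "Age, gender and SPPB will be adjusted for in the statistical analysis". Arm is not in that list.
- **Trial design:** the sub-study hypothesis is that "the REACT intervention will slow the rate of brain atrophy and of decline in cognitive function".

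**The concern.** By the sub-study's own hypothesis, arm influences both change scores. Suppose the exercise arm loses less hippocampal volume and also declines less on memory. Its participants then sit, on average, higher on both axes than the controls. A single coefficient over everyone picks up that separation even if, within each arm, a person's hippocampal change says nothing about that person's memory change. The better the intervention works on both measures, the larger this component becomes.

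What is at stake is interpretation. A hippocampus–memory correlation from an exercise trial invites the reading that people whose hippocampus is better preserved keep their memory better. A coefficient that ignores arm cannot separate that from two unrelated treatment effects. The plan has group in the model for hippocampal change and names ANCOVAs for the cognitive outcomes, but names no such term when the two changes are related to each other.

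**Working it through.** **Plan's own figure.** There is none to reproduce. The article gives no sub-study size, expected effect or expected correlation for this analysis, so everything below rests on stated assumptions.

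**Inputs.**
- Share in the intervention arm, p: 1/2 under the main-trial 1:1 allocation and 2/3 under the pilot 2:1 allocation (Randomisation/allocation section).
- Effect of arm on each change score, d, in within-arm SD units and in the favourable direction for both: assumed 0.3, 0.5, 0.8 and 1.0.
- Within-arm correlation: assumed zero, so that any non-zero result is due to arm alone.
- Sub-study size N: assumed 60, 100 and 200.

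**Step 1: correlation induced by arm alone.** With equal effects on both measures,

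r = d²·p(1−p) / [1 + d²·p(1−p)]

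At p = 1/2, p(1−p) = 0.25:

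| d | calculation | r |
|---|---|---|
| 0.3 | 0.0225 / 1.0225 | 0.022 |
| 0.5 | 0.0625 / 1.0625 | 0.059 |
| 0.8 | 0.16 / 1.16 | 0.138 |
| 1.0 | 0.25 / 1.25 | 0.200 |

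At p = 2/3, p(1−p) = 0.222 and d = 0.5 gives 0.0556 / 1.0556 = 0.053. The pilot allocation changes little.

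**Step 2: how often such a coefficient would cross a nominal two-sided 5% line, if one were applied.** Fisher's z has mean atanh(r)·√(N−3). For d = 0.5 and N = 100 this is 0.0589 × 9.849 = 0.58, and Φ(0.58 − 1.96) + Φ(−0.58 − 1.96) = 0.089.

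| d | N = 60 | N = 100 | N = 200 |
|---|---|---|---|
| 0.3 | 5.3% | 5.5% | 6.1% |
| 0.5 | 7.3% | 8.9% | 13.1% |
| 0.8 | 18.2% | 27.7% | 49.5% |
| 1.0 | 33.4% | 51.5% | 81.2% |

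**Step 3: would the general age, gender and SPPB adjustment deal with it?** A plain Pearson coefficient has no covariates, so that sentence can reach this analysis only if the method becomes a partial correlation or a regression. Even then arm is not in the list. In simulation (8,000 runs per scenario; arm effect 0.5 SD on both measures; age correlated either 0 or 0.3 with both changes), adjusting for age alone left 7% to 13% of runs significant at nominal 5%. Adjusting for arm and age gave about 5% (4.9% to 5.5%) in every scenario.

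**Step 4: the covariate lists side by side.** The ANCOVA for hippocampal change uses group, age group, gender and education. The general sentence lists age, gender and SPPB. The correlation sentence lists nothing. The three do not agree on what this analysis adjusts for.

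**The case against.** The strongest case on the other side is that one descriptive sentence is being read as a full specification.

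- **Pooling is not stated.** The plural would fit within-arm correlations, which carry no arm effect. This stands: the problem is conditional on calculating over all participants. That is the natural reading of a sentence that mentions no split, but the text does not fix it.
- **No test is promised.** The text speaks of examining and calculating. This also stands, so the rates in Step 2 only illustrate scale. The shift in the coefficient remains whether or not a p value is attached.
- **No mechanism is claimed.** The process evaluation names mediation analyses where mechanism is intended; the correlation sentence does not. This is fair, and it is a reason to label the result explicitly as an association.
- **Unadjusted results are acceptable elsewhere in the plan.** Hippocampal change is first analysed by ANOVA without covariates. But that ANOVA still contains group; the correlation does not.
- **An article condenses a fuller protocol.** Detail may sit there, and omitted detail is no finding. Here, though, the article names the method, and that method cannot carry the adjustment that the same sub-study section promises.

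A reader might also infer that age is simply left out, or that ageing alone would create the association. The documents do not support either. Model assumptions says age will be adjusted for. A decline common to everyone shifts the means and induces no correlation; only age differences between people that relate to both rates of change would do so, and the article gives no figures for these. For scale, if age correlated 0.3 with each change, the induced r would be 0.3 × 0.3 = 0.09.

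**Conclusion.** The point holds in a limited form. The article fixes plain Pearson's correlations of two change scores and nowhere adjusts them for or splits them by arm, while hypothesising that the intervention affects both. If the arms are pooled, the coefficient mixes any within-person link with parallel treatment effects. Under 1:1 allocation and no within-arm link, the treatment-induced part is about 0.06 for 0.5 SD effects on both measures and 0.14 for 0.8 SD, and is negligible at 0.3 SD or below. These effect sizes are assumptions; the article gives none.

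It would go too far to say that the plan will produce a spurious significant finding. With 0.5 SD effects acting alone, the rate at nominal 5% is only about 7% to 9% for N of 60 to 100. Much higher rates need large arm effects, strong age correlations, or several such sources added together. The correlation sentence and the general adjustment sentence do need reconciling. This is a secondary analysis in a nested sub-study; neither the trial's primary outcome nor the sub-study's is affected.

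**What to change.** Replace the correlation sentence with one that names a method able to carry covariates, for example: *The association between the two changes will be estimated by a partial correlation (or a regression of memory change on hippocampal change) adjusted for arm, age, gender, education and SPPB. Within-arm correlations will be shown alongside, and the result will be described as an association.* Then align the sentence in Model assumptions so that it is clear which covariates apply to this analysis and that arm is among them.

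The cost is one or two sentences and a few degrees of freedom. Every covariate is already named in the plan. Continuous age or the baseline values of both measures could be added, but that is a matter of preference and not needed to resolve the point.

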#### Data presentation and analysis models

Continuous outcomes will be summarised by means and SDs (or medians and interquartile ranges (IQRs) if distributions are skewed). Categorical outcomes will be presented as numbers and percentages of patients in each category. Binary outcomes will be presented as numbers and percentages of patients in the category of interest.

#### Model assumptions

For all methods outlined, underlying assumptions will be checked using standard methods, e.g. residual plots. If assumptions are not valid then alternative methods of analysis will be sought. In particular, the underlying assumption of the linear impact of baseline covariates will be assessed and, if necessary, baseline covariates will be categorised and fitted as factors in the model. Age, gender and SPPB will be adjusted for in the statistical analysis.

#### Subgroup analyses

We will compare response to exercise based on SPPB score (ranges 4–7 and 8–9), adherence (high-low), age categories (65–74, 75 + years), gender and cognition (MoCA < 26 > 26, 26 + years).

### Economic evaluation

The economic evaluation will estimate the cost-effectiveness of the REACT intervention compared to control, for older people with major mobility limitations, from the perspective of the NHS and Social Care Services.

Using data collected within trial we will estimate the resource use and costs associated with delivery of the intervention, and the wider NHS-, social care- and participant-level resource use and costs over a 24-month follow-up. The primary component of resource use for delivery of the intervention is the time input (contact and non-contact time) for REACT trainers, and data will be collected on each activity by the trainer over the delivery of the intervention for each group, and across each phase of intervention delivery. Other areas of resource use (e.g. training, set-up, facility costs, cost of pedometers) will be recorded within trial by the trial coordinator. Data on use of health-, social care- and other participant-related resource use will be collected, using a participant self-report resource use questionnaire, at baseline, 6, 12 and 24 months. Data on resource use will be combined with national unit cost data obtained from available sources including Personal Social Services Research Unit (PSSRU) and NHS reference costs to estimate costs over the 24-month follow-up [26, 27]. The primary economic outcome measure will be the quality-adjusted life years (QALYs) derived from participant-reported EuroQoL five-dimension, five- level (EQ-5D-5 L) data, applying the area-under-the-curve approach [28], collected alongside the resource use questionnaire and using the UK tariff (presently recommended by NICE [29]). Data on estimated costs and QALYs by group will be presented, together with incremental QALYs and incremental costs, to present a policy-relevant cost-effective analysis (CEA).

Analysis will follow established methods for the conduct of economic evaluation in health technology assessment [30] and will be consistent with recommendations from NICE (UK) on ‘reference case’ cost-effectiveness analyses [31]. Findings will be reported in keeping with the CHEERS guidelines for cost-effectiveness studies [32]. CEA will be presented using base case estimates and uncertainty will be considered via detailed one-way and multi-way sensitivity and scenario analyses. The non-parametric nature of the distribution of resource use and cost data will be addressed using bootstrapping methods for estimation of confidence intervals around estimates of mean costs and incremental cost-effectiveness ratios (ICER). Results will include disaggregated data, as well as synthesis of costs and outcome data, and will include presentation of cost-effectiveness plane and cost-effectiveness acceptability curves to describe the likelihood of cost-effectiveness at different cost-effectiveness thresholds [33, 34].

To address missing data on costs and outcomes, multiple imputation will be used for making the assumption that the data are missing at random [35]. Given the longer-term nature of potential benefits from the REACT intervention, we will conduct evidence synthesis and decision-analytic modelling to assess the longer-term (lifelong) consequences of the intervention vs. control, including consequences in terms of health and social care costs.

